### Sample size and power calculation

A total sample size of between 720 and 961 older adults is needed to compare volume of social support service use between clients using the ACPQ/ICECAP-O assessment tools (cases) and a matched sample of those who are not assessed (controls) using general linear modelling (80 and 90% power, respectively). This sample size estimate assumes an R-squared value of 0.1 for the full model and inclusion of up to 10 covariates. A sample size of between 830 and 1110 clients is needed in each of the case and control groups to detect a 15% risk reduction in entry into residential aged care with a 12-month follow-up period (80 and 90% power, respectively).

For the interviews and focus groups, it is estimated that a sample size of 30 community aged care clients and 30 staff will achieve data saturation (i.e. no new themes are emerging). These estimations are based on earlier studies conducted by the research team in this area [31].

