#### Community aged care staff

Prior to data collection, the research team will provide all community aged care staff that complete needs assessments within the three study regions with training in the administration and purpose of the ACPQ and ICECAP-O. Community aged care staff will then complete the ACPQ and ICECAP-O with all their clients during routine needs assessments. Approximately 30 staff will be invited to participate in interviews and focus groups during training and feedback sessions with the research team to gain an insight into their perspectives regarding acceptability of the ACPQ and ICECAP-O, their experiences in using the tools (research question two), and the perceived impact the tools have on client discussions and service provision (research question three).

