##### Data analyses

The first part of the analysis for this research question aims to determine whether the actions identified by staff following administration of the tools result in a change in social participation and QoL scores at 12-monthly follow-up needs assessments. Individual growth modelling will be used to examine changes over time in social participation and QoL scores for all older adults who are administered the tools at two or more-time points.

The second part of the analysis will use case-controlled analyses to determine whether the implementation of the tools increases the volume of social support service use and improves outcomes. A control group of clients who do not receive the tools will be identified from the data on all community care clients extracted by Uniting. Each person who receives the tools will be matched to a person who does not receive the tools, based on their sociodemographic and service use characteristics at the time of their routine reassessment. Propensity score matching methods will be used to reduce the impact of confounding and selection bias that can occur in observational studies [44]. Volume and frequency of services following routine assessment will be compared between case and control groups using general linear modelling. Time to entry into residential aged care and frequency of adverse events (e.g. hospitalisations) will be compared between case and control groups using competing risks regression and negative binomial regression, respectively.

Interview and focus group data will be analysed as outlined earlier in Research Question Two.

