### Limitations

This study will use an iterative approach to allow for review and changes to the implementation process across the three waves. This approach will allow for greater understanding of the data and improvements that will help to strengthen the implementation process over time. One limitation of this approach is the inability to control for all factors due to changes made at each wave. However, the aim of this study is to evaluate the implementation of the ACPQ and ICECAP-O so the ability to be able to review and adjust this process is required. The quantitative analyses will also account for the clustered nature of the data within each wave.

Focus groups and interviews with Uniting staff and clients will produce indicative and rich data about social participation and the implementation of the ACPQ and ICECAP-O. All staff and clients that complete both tools will be invited to participate in this process to help ensure a representative sample is used. However, participation in this element of the study is voluntary and the data collected are based on the perceptions of the participants, which could potentially limit the generalisability of the findings from this study.

Similar to other studies conducted with older adults, there is a potential limitation associated with sample size and high attrition rates. Relocation to residential aged care and mortality are attrition risks in research involving community aged care clients. However, this study will be undertaken in partnership with one of the largest aged care providers in Australia. Targeting both new and existing clients across Uniting’s large client population will allow for statistical power to be optimised, as well as the potential to explore the impact of the intervention on specific vulnerable groups.

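### The sample sizes show no allowance for clustering, although the tools are rolled out by region and assessor and the analysis is to account for clustering; without such an allowance, the stated 80% and 90% power is too high

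*Protocol article*

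**What the plan says.** Under Sample size and power calculation, the protocol article gives two sets of figures.

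- **Service volume:** "A total sample size of between 720 and 961 older adults is needed to compare volume of social support service use" between cases and matched controls, "using general linear modelling (80 and 90% power, respectively". The listed basis is: "This sample size estimate assumes an R-squared value of 0.1 for the full model and inclusion of up to 10 covariates".
- **Residential care entry:** "A sample size of between 830 and 1110 clients is needed in each of the case and control groups". The target here is a 15% lower risk over 12 months, again for 80% and 90% power.

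Exposure is not set client by client. The Methods section defines a wave by a region chosen in advance, and there are three. Under Community aged care staff, training goes to "all community aged care staff that complete needs assessments within the three study regions", who then use the tools with every client they assess. Under research question three, Data analyses, "Each person who receives the tools will be matched to a person who does not receive the tools". Controls come from the provider's whole client base, and region is not named among the matching characteristics.

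The Limitations section adds: "The quantitative analyses will also account for the clustered nature of the data within each wave".

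**The concern.** Clients in one region share local services and referral practice. Clients of one assessor share the person who turns the tool results into a care plan. Service volume and residential care entry may therefore be correlated within regions and within assessors. Where exposure differs between those clusters, positive correlation widens the standard error of the case-control difference.

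The article promises an analysis that recognises this, but the assumptions listed for the sample sizes do not. If clustering was left out of the sizing and is then modelled, the stated power is not there. If it is left out of both, the confidence intervals are too narrow. In the first case, a null result on services or residential care could be read as coming from a study with 80% or 90% power when it was not.

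**Working it through.** **1. Can the plan's own figures be reproduced?** Not uniquely. The significance level, the tested effect of exposure and the control event rate are not stated. I assume two-sided 0.05 and solve for the rest.

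- *Service volume.* Test of one exposure term in a multiple regression, with noncentrality N × ΔR²/(1 − R²) and R² = 0.1. A round ΔR² of 0.01 gives 709 and 948. The stated 720 and 961 correspond to ΔR² of about 0.0098 to 0.0099.
- *Residential care entry.* Two proportions, 15% relative reduction, no continuity correction. A control risk of about 45.2% gives 830 and 1110 per group.

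Both fits use a design effect of 1, but they do not show that 1 was used. With a design effect of 1.5, ΔR² of about 0.0148 also gives about 720 and 961, and a control risk of about 0.56 gives about 830 and 1110. With a design effect of 2, ΔR² of about 0.0197 and a control risk of about 0.635 do the same. An inflation factor multiplies the 80% and 90% sizes alike, so the stated pairs cannot reveal it.

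**2. What would clustering do to the stated sizes if no allowance was made?** The formulas are:

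- Design effect: DE = 1 + (m − 1) × ICC, with m clients per cluster.
- Power = Φ[(1.96 + z)/√DE − 1.96], with z = 0.842 for nominal 80% and 1.282 for nominal 90%.

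The ICCs are assumptions. So is the structure: exposure differs wholly between three exposed and three control regions of equal size.

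Worked example: 720/6 = 120 per region. At ICC 0.01, DE = 1 + 119 × 0.01 = 2.19, and power = Φ(2.802/1.480 − 1.96) = Φ(−0.07) = 47%.

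| Comparison | m | ICC | DE | Nominal power | Power |
|---|---|---|---|---|---|
| Service volume, N = 720 | 120 | 0.001 | 1.12 | 80% | 75% |
| | | 0.005 | 1.59 | 80% | 60% |
| | | 0.01 | 2.19 | 80% | 47% |
| Service volume, N = 961 | 160 | 0.001 | 1.16 | 90% | 85% |
| | | 0.01 | 2.59 | 90% | 52% |
| Residential care, 830 per group | 830/3 = 277 | 0.001 | 1.28 | 80% | 70% |
| | | 0.01 | 3.76 | 80% | 30% |
| Residential care, 1110 per group | 1110/3 = 370 | 0.001 | 1.37 | 90% | 79% |
| | | 0.01 | 4.69 | 90% | 32% |

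**3. Clustering by assessor alone.** The article gives no caseload, so I assume 20 clients per assessor. ICC 0.01 gives DE = 1.19, and ICC 0.05 gives DE = 1.95. Power is 73% and 52% at N = 720, against 80%. It is 84% and 64% at N = 961, against 90%.

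These figures use normal critical values. With as few as six regions, a small-sample reference distribution would lower region-level power further.

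**The case against.** **The article is condensed.** The sample-size section is one paragraph that also omits the significance level and the control event rate, and a fuller document may hold a design effect. This stands in part: independence is inferred, not stated. But the article does list the assumptions behind its power and, separately, promises a clustered analysis. A reader cannot tell whether the two agree.

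**The numbers prove that no inflation was used.** A reader might infer this from the close match to unclustered formulas. The documents do not support it: as shown above, design effects of 1.5 or 2 fit as well with another unstated input.

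**The analysis will treat the three waves as its clusters.** A reader might take the Limitations sentence this way and conclude that inference rests on three units. The wording can equally mean staff or sites nested inside waves, so this is a point to clarify, not an error.

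**The region-level loss is exaggerated.** The design-effect formula assumes that exposure differs wholly between clusters. The article does not exclude controls from the study regions, for example clients not yet reassessed, and matching on prior service use may lower the residual correlation. Both would shrink the loss. Since trained staff use the tools with all their clients, however, overlap within an assessor may be limited.

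**The sizes are minimums.** Under research question one, 720 to 961 is called a minimum, and the provider had over 6800 clients in 2016. The table therefore describes the stated sizes, not the power the study will achieve. Extra clients in the same three exposed regions add little against region-level correlation.

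**Conclusion.** The point holds in conditional form. The article attaches 80% and 90% power to sizes whose listed assumptions contain no clustering term, while it describes rollout by region and assessor and promises an analysis that accounts for clustering. If no allowance was made, power is overstated under any positive ICC between exposed and control clusters.

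The size of the loss cannot be fixed from the documents, which give no ICC, cluster size or number of control regions. Under the region-level assumptions above, even an ICC of 0.001 takes 80% power to 75% or 70%, depending on the comparison, and 0.01 takes it to 47% or 30%. These are illustrations and not estimates of this study's power. The finding is that the sizing and the promised analysis have not been reconciled, not that a calculation has been shown to be wrong.

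**What to change.** - **Power.** Restate it for both comparisons with an explicit design effect, and give the significance level, the tested effect and the control event rate alongside. Estimate the ICCs for service volume and residential care entry from CareLink+ data where identifiers allow. The article does not list an assessor or outlet identifier, and Additional file 2 is not shown, so this needs checking. Failing that, show power over a stated ICC range. Enrolment need not rise.
- **Clustering level.** For the case-control analyses, name it as assessor or service outlet nested within wave/region, with a small-sample correction, rather than the three waves themselves.
- **Region effects.** Use region fixed effects only where a region contains both cases and controls. Elsewhere they cannot be separated from exposure.

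The cost is a recalculation and a few sentences. The downside is that the stated power becomes less favourable.

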## Discussion

This paper has described the methods that will be utilised to evaluate the implementation of social participation and QoL assessment tools (ACPQ and ICECAP-O) in community aged care. It is anticipated that this intervention will enhance the provision of targeted services, and thus increase social participation and QoL for older adults living in the community setting. By using a mixed method approach, this study allows for the collection of qualitative data that provides rich insights into community aged care clients’ and staff experiences. Adopting ACPQ and ICECAP-O tools into routine needs assessments for community aged care clients is a potentially simple and effective way to gain understanding into older adults’ levels of social participation and QoL. Community aged care staff can use this information to discuss future strategies to increase social participation and QoL with their clients. This project will also provide the opportunity to consider the validity and reliability of the ACPQ and ICECAP-O among community aged care clients in Australia.

### Strategies to increase validity and reduce bias

By using an iterative, multi-method design for this study, the different approaches will be used as a form of validation of the implementation process used. The methods that will be utilised to address the study objectives include the collection and analysis of quantitative data from the CareLink+ database, interviews and focus groups to understand staff and client perceptions of social participation and the implementation of the tools, and adaptation of the implementation process at each wave based on staff feedback during training and feedback sessions. The use of methodological triangulation will help to reduce bias and deficiencies associated with using a single method design [45]. Steps will be taken to check the representation of older Australians within the study sample through comparison of demographic data from the study population and older adults living within NSW and the ACT.

Uniting community aged care staff will be provided with training and feedback by the research team on how to administer the ACPQ and the ICECAP-O tools prior to implementing the tools with clients. The training will include information on how to access the forms via the Uniting care management system (CareLink+) and how to ask the questions effectively. During each wave the Working Group Committee will review the data and forward any issues and resolutions to staff as required during the succeeding waves.

### Limitations

This study will use an iterative approach to allow for review and changes to the implementation process across the three waves. This approach will allow for greater understanding of the data and improvements that will help to strengthen the implementation process over time. One limitation of this approach is the inability to control for all factors due to changes made at each wave. However, the aim of this study is to evaluate the implementation of the ACPQ and ICECAP-O so the ability to be able to review and adjust this process is required. The quantitative analyses will also account for the clustered nature of the data within each wave.

Focus groups and interviews with Uniting staff and clients will produce indicative and rich data about social participation and the implementation of the ACPQ and ICECAP-O. All staff and clients that complete both tools will be invited to participate in this process to help ensure a representative sample is used. However, participation in this element of the study is voluntary and the data collected are based on the perceptions of the participants, which could potentially limit the generalisability of the findings from this study.

Similar to other studies conducted with older adults, there is a potential limitation associated with sample size and high attrition rates. Relocation to residential aged care and mortality are attrition risks in research involving community aged care clients. However, this study will be undertaken in partnership with one of the largest aged care providers in Australia. Targeting both new and existing clients across Uniting’s large client population will allow for statistical power to be optimised, as well as the potential to explore the impact of the intervention on specific vulnerable groups.

## Abbreviations

ACPQ: Australian Community Participation Questionnaire
ACT: Australian Capital Territory
ADLs: Activities of Daily Living
COREQ: COnsolidated criteria for REporting Qualitative research
ICECAP-O: ICEpop CAPability Measure for Older Adults
NSW: New South Wales
QoL: Quality of Life
RECORD: Reporting of studies Conducted using Observational Routinely-collected health Data
